## Abstract

**Introduction:**

Warfarin has frequently been underused in older people for stroke prevention in atrial fibrillation (AF). Direct oral anticoagulants (DOACs) entered the UK market from 2008 and have been recommended as an alternative to warfarin. This study aimed to describe any changes in the prescribing of oral anticoagulants (OACs) to people aged ≥75 years in UK general practice before and after the introduction of DOACs, to examine differences in patient characteristics which may influence prescribers’ decisions regarding anticoagulation, to evaluate the time people stay on OACs and switching between OACs.

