### Covariate classification

It is recognised that some patients may remain in the cohort for a long time and their covariates may change. Therefore, covariates will be identified separately for each of the time periods the patient contributes data and will be grouped by DOAC, warfarin or no OAC, depending on exposure for that period.

We want to investigate whether certain comorbidities influence the prescribing of OACs. We will therefore look for comorbidities accumulated up to the end of the time period for patients who do not receive an OAC or the OAC index date where one is prescribed. Patients will be classified as having a comorbidity if the patient record contains ≥1 diagnostic Read code for a disease or ≥3 Read codes supporting the presence of the disease at any time prior to the relevant date for that period. Read codes used to support the presence of disease include attendance at specialist clinics (eg, diabetes clinics) or codes related to follow-up, such as hypertension monitoring.

Concomitant medication will be classified as≥1 prescription issues for a medication of interest in the 3 months prior to study entry, commencing an OAC, or the end of the time period. We will describe medications at study entry as baseline and then in each time period for the no OAC and incident OAC patients as described for the comorbidities previously mentioned. The medications of interest affect either stroke or bleeding risk or commonly interact with OACs (antihypertensives, antiplatelets, statins, diabetic medications, antiarrhythmics, non-steroidal anti-inflammatory drugs, corticosteroids, anticonvulsants, systemic azoles, HIV protease inhibitors and ciclosporin).

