#### ​HAS-BLED

International guidelines recommend using this score to assess the risk of bleeding with anticoagulants.^3–5^ Higher scores indicate an increased risk of bleeding with anticoagulants. The presence of each disease scores one point and the maximum score is 9. For the purpose of this study, the maximum score for the HAS-BLED will be 8. The L in HAS-BLED corresponds to labile INR defined as a time in therapeutic range with warfarin of less than 60%. As INRs are not recorded consistently in the CPRD and because people prescribed DOACs would not have INR tests at all, this element of the score will not be included. Definitions for each element were based on those described by Pisters and colleagues^18^ but have been adapted to suit the information recorded in the CPRD.

*Hypertension (1 point*): as described for CHA_2_DS_2_-VASc score previously.

*Abnormal renal or hepatic function (1 point each, maximum of 2 points*): renal and hepatic function will be determined using a combination of clinical Read codes and test results.Renal impairment: includes chronic dialysis, transplant and chronic renal impairment (defined as stage 3 or above, moderate, severe or end stage). If renal impairment is recorded with no severity but there is a test result for creatinine of ≥200 µmol/L, the patient will be allocated a point. If there are no test results recorded, the patient will score 0. Codes for renal disease where it does not state that renal function is impaired will be excluded.Hepatic disease: includes chronic hepatic disease (cirrhosis, hepatitis, fatty liver and fibrosis), liver transplantation or biochemical evidence of significant hepatic derangement (bilirubin>2× upper limit of normal in association with aspartate aminotransferase/alanine aminotransferase/alkaline phosphatase) where these blood test results are recorded in CPRD.
*Stroke (1 point*): as described for CHA_2_DS_2_-VASc score previously.

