*Bleeding history or predisposition (1 point*): includes any previous bleed; categorised based on the International Society of Thrombosis and Haemostasis guidance as major bleeding where the bleed occurs in a critical area or organ or requires a blood transfusion (CPRD does not state the number of units infused, so any requirement for a blood transfusion in conjunction with a Read code for bleeding will be classified as a major bleed)^19^; or clinically relevant non-major bleeding (defined as a bleed not fitting the major bleed criteria but requiring review by a healthcare professional, as the codes are recorded by a GP we will assume that these bleeds required review)^20^; excludes codes for traumatic bleeding, bleeding related to pregnancy and postoperative bleeding. Predisposition to bleeding includes anaemia and gastric, duodenal and peptic ulcers.

*Elderly (1 point*): defined as being aged >65 years old.

*Drugs or alcohol (1 point each, maximum of 2 points*): a point will be allocated where a patient receives a prescription for an antiplatelet or non-steroidal anti-inflammatory medication within the time period. Exact alcohol consumption is not well documented in the CPRD, but patients will score a point for this element if they have any record stating the number of units consumed per week as >8 units or if they have any codes for heavy/problem drinking.

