#### ​Objective 2: to describe switching between OACs during the study period

The number and percentage of patients switching from warfarin to DOAC, DOAC to DOAC and DOAC to warfarin will be calculated. The number of patients with multiple switches and details of the switches will be described. The average time to switch will be reported.

#### 
*​*Objective 3: to compare the characteristics of patients with AF who were newly started on OACs during each period described in objective 1, to those who were not prescribed anticoagulation in the same period

Demographics, characteristics, comorbidities and concomitant medications will be reported for the three time periods described. Prevalent OAC users will be excluded from this part of the study as we want to compare those started on an OAC with those who are not during each time period.

Patients may contribute data to more than one group, but they will be censored at the time they are prescribed their index OAC. For example, they may enter the study during the first time period but may not be prescribed an OAC until period 3. In this case, they would contribute data to the no-OAC group in time periods 1 and 2 and then one of the OAC groups in period 3. If they entered in period 1 and started on an OAC in period 2, they would contribute data to the no OAC group in period 1 and the OAC group in period 2; they would not contribute any data to period 3 as they would be censored. Figure 3 illustrates how patients contribute to different groups during their time in the study. Patient demographics (age and biological sex) and characteristics (BMI, smoking status and alcohol consumption) will be reported as percentages in predefined categories. The proportion of the cohort with each of the comorbidities and concomitant medications will be described. The mean CHA_2_DS_2_-VASc and HAS-BLED scores will be reported.

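### In Objective 3 the HAS-BLED drug point for no-OAC patients can include antiplatelets prescribed after, or in place of, anticoagulation, so part of a group difference in mean score may follow from the decision it is meant to inform

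*Protocol article*

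**What the plan says.** **Purpose.** The abstract's introduction gives as one aim "to examine differences in patient characteristics which may influence" the prescriber's decision on anticoagulation. Covariate classification and the Discussion describe the covariates in similar terms.

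**Comparison.** Under Statistical analysis, Objective 3, the comparator is patients left without an OAC in the same period: "Prevalent OAC users will be excluded from this part of the study as we want to compare those started on an OAC with those who" (quoted in part). Starters are censored at their index OAC. Mean HAS-BLED is reported.

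**Score.** The HAS-BLED section adapts the published score: "For the purpose of this study, the maximum score for the HAS-BLED will be 8", because labile INR is left out. For the drug element, "a point will be allocated where a patient receives a prescription for an antiplatelet or non-steroidal anti-inflammatory medication within the time period".

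**Reference dates.** Covariate classification reads comorbidities "up to the end of the time period for patients who do not receive an OAC or the OAC index date where one is prescribed". Concomitant medication, which includes antiplatelets as a class of its own, is read "in the 3 months prior to study entry, commencing an OAC, or the end of the time period".

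**The concern.** A covariate put forward as a possible reason for a decision should not be able to result from that decision. The antiplatelet part of the drug point does not meet this condition in the no-OAC group. If a prescriber decides against an OAC and an antiplatelet is prescribed afterwards or instead, the patient gains a point because of the decision. A starter's antiplatelet prescriptions after the index OAC do not count.

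A higher mean HAS-BLED in untreated patients could then be taken to show that bleeding risk held prescribers back, when some of the difference is treatment received. The reading has consequences beyond the table. Objective 4 adjusts for covariates that Objective 3 shows to be important, and the Discussion expects the results to point later studies to potential confounders.

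**Working it through.** **1. The scale.** The plan's maximum is reproduced from its own elements: hypertension 1, renal or hepatic 2, stroke 1, bleeding 1, elderly 1, drugs or alcohol 2.

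1 + 2 + 1 + 1 + 1 + 2 = 8, as stated (9 with labile INR).

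Everyone is at least 75 at entry, so the elderly point is the same for all and 8 − 1 = 7 points can vary. The antiplatelet/NSAID point is one of these 7.

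**2. What can count in each group.** This reads the Objective 3 censoring rule as applying to the drug point; the HAS-BLED sentence itself does not mention the index date.

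| | No OAC in the period | OAC starter |
|---|---|---|
| Prescriptions counted | All while under observation in the period (up to 5 years) | Those in the period before the index OAC |
| Can include an antiplatelet given after or instead of anticoagulation | Yes | Only one given during earlier untreated time in the period |

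No rule separates antiplatelet use that preceded the decision from use that followed it.

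**3. Size.** The protocol gives no antiplatelet rates, so all inputs here are assumptions:
- s: share of no-OAC patients given an antiplatelet because no OAC was given
- s0: the same share among starters, during their untreated time
- q: share of those patients who would have had the drug point anyway, set at 30% in both groups

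Shift in the no-OAC mean = s × (1 − q). Shift in the starters' mean = s0 × (1 − q). Shift in the group difference = (1 − q) × (s − s0) = 0.7 × (s − s0).

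| s | s0 = 0 | s0 = 10% | s0 = 20% |
|---|---|---|---|
| 20% | 0.14 | 0.07 | 0.00 |
| 40% | 0.28 | 0.21 | 0.14 |
| 60% | 0.42 | 0.35 | 0.28 |

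With q = 0 and s0 = 0 the values would be 0.20, 0.40 and 0.60. If s0 exceeded s, the sign would reverse.

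**4. Would a common look-back window remove it?** No. If both groups used the 3 months before the reference date, a no-OAC patient's last 3 months could still contain an antiplatelet given in place of an OAC. The long window adds to the problem but is not the whole of it.

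**5. Does the planned antiplatelet row show it?** Only roughly. That row uses 3 months and the score uses the period, so the row cannot be subtracted from the mean score.

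**The case against.** The case on the other side is substantial, and most of it limits the point without removing it.

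- **Substitution is not in the documents.** Nothing in the protocol says that antiplatelets are given instead of an OAC; they appear only among drugs that affect stroke or bleeding risk or interact with OACs. This stands. What the protocol does establish is that its counting rule admits such prescriptions in one group and largely excludes them in the other.
- **Labile INR.** A reader might infer that the protocol contradicts itself by dropping labile INR as treatment-dependent while keeping antiplatelets. The text does not support that. It cites inconsistent INR recording and adds that "because people prescribed DOACs would not have INR tests at all, this element of the score will not be included". Both reasons concern whether the element can be measured, and antiplatelet prescriptions can be measured in every group.
- **Starters have untreated time too.** This stands, and it is why the shift depends on s − s0. A reader might take 0.14 to 0.42 as the bias in the comparison; it is only the limit when s0 is zero and q is 30%.
- **The score does what it is defined to do.** An antiplatelet raises HAS-BLED whatever the reason for it. It would therefore be wrong to say that the no-OAC mean could move with no change in bleeding risk as the score defines it. The difficulty lies in using the score to explain non-treatment.
- **Objective 3 is descriptive and already reports antiplatelets.** True. No planned conclusion says that bleeding risk deterred prescribers. The stated purpose nevertheless invites that reading, and the Discussion's limitations do not mention the problem.

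**Conclusion.** The point holds as a limit on interpretation that is cheap to address. As written, the no-OAC group's drug point can contain prescribing that follows the decision not to anticoagulate, so a difference in mean HAS-BLED cannot be read wholly as a difference in prior bleeding risk. The shift in the group difference is 0.7 × (s − s0), at most 0.14 to 0.42 points on the 8-point scale for s of 20% to 60%, with s, s0 and the 30% all assumed. The actual size cannot be derived from the protocol and may be small.

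A reader might go further and conclude that the element is wrongly scored, or that the full score should give way to a reduced one as the basis of the comparison. Neither follows. Antiplatelets are an element of the score that the protocol says guidelines recommend, and dropping them also discards genuine antiplatelet use from before the decision. The reduced score is a companion to the full one, not a correction of it.

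**What to change.** 1. Keep the full 8-point HAS-BLED as planned.
2. Beside it, for each group and period, report HAS-BLED without the antiplatelet element, so that the drug point is given for NSAIDs only.
3. State in Objective 3 that bleeding risk will be interpreted as a possible influence on non-treatment only where the two scores agree. Where they diverge, report the divergence and draw no such inference.
4. Describe the already planned antiplatelet row in the no-OAC group as treatment received, which may follow from the decision.

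The cost is one extra column from data already being extracted. The small downside is that this column is not the published score, which is why the full score stays beside it.

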#### ​Renal impairment

DOACs are predominantly renally cleared and so require dose adjustment and careful monitoring in renal impairment. The elimination of warfarin is mostly metabolic, being metabolised by hepatic enzymes so it is not affected by changes in renal function. Renal impairment may therefore affect the decision of which anticoagulant (if any) to use so it has been included as a covariate alone, in addition to its inclusion in the HAS-BLED score. The Read code or test result dated closest to the relevant date for the period will be used to categorise the presence and level of renal impairment.

##### Chronic renal impairment

Includes chronic dialysis, renal impairment and chronic kidney disease regardless of whether severity or stage is reported. Test results for creatinine and estimated glomerular filtration rate (eGFR) will also be obtained where available. If test results are available, they will be used to classify whether a patient has renal impairment and the stage of impairment (if eGFR is documented). Codes for a renal disease that may reduce kidney function but with no test or diagnostic code to support the presence of renal impairment will be excluded.

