#### ​Objective 4: to describe persistence with DOACs compared with warfarin

Duration of prescribing of DOACs will be compared with warfarin using Cox proportional hazards, stratified by DOAC and adjusted for age and other important covariates identified in objective 3. All incident OAC users will be included. Time on OAC will be calculated as the difference between the discontinuation date of the OAC and the index date, as defined previously. Patients will be censored at the outcome (discontinuation of OAC therapy), on the date they stop contributing research standard data or the date of death.

All analyses will be conducted in STATA V.15.^24^ All values will be reported with 95% CIs.

#### 
*​*Missing data

There is likely to be a substantial amount of missing data for weight, BMI, smoking status and alcohol consumption as these variables may not be regularly updated by GP practices. We will use logistic regression to ascertain whether other variables (age, sex or comorbidities) predict whether these data are missing. If these variables do not predict the missing data, then we will assume that the data are missing at random. The proportion of missing data for these variables will be presented. If the data are missing at random, we will impute the missing values using multiple imputation and conduct a sensitivity analysis to investigate the effect of the missing data on the results of the analyses. However, previous studies suggest it may only be appropriate to impute weight and BMI.^25 26^

## 
*​*Patient and public involvement

Patients and the public were not involved in the production of this protocol or in the design of the study.

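### Patients with neither a renal test nor a renal code default to unimpaired, and ascertainment may be more complete in DOAC starters than in untreated patients

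*Protocol article*

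**What the plan says.** The stand-alone renal covariate is defined in the protocol article under Renal impairment and Chronic renal impairment. There are two routes to being classed as impaired.

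- **Code.** "Includes chronic dialysis, renal impairment and chronic kidney disease regardless of whether severity or stage is reported". A diagnostic code is therefore enough without a test.
- **Test.** "Test results for creatinine and estimated glomerular filtration rate (eGFR) will also be obtained where available". When a result is on file it settles whether impairment is present, and a documented eGFR also gives the stage. A test can rule impairment in or out.

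Codes for kidney disease with neither a test nor a diagnostic code of impairment behind them are excluded. The record nearest the relevant date is used, and no look-back window is given. Covariate classification sets that date as the OAC index date for starters and the end of the time period for patients who receive no OAC.

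Objective 3 reports the share of the cohort with each comorbidity. The Missing data section says "There is likely to be a substantial amount of missing data for weight, BMI, smoking status and alcohol consumption" and plans a check of predictors of missingness, and possibly imputation, for those variables. It does not name creatinine or eGFR.

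On the link with treatment, the Renal impairment section says "DOACs are predominantly renally cleared and so require dose adjustment and careful monitoring in renal impairment", and describes warfarin elimination as unaffected by renal function. It includes the covariate because renal function may influence which anticoagulant, if any, is chosen.

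**The concern.** The plan has no place for a patient whose renal status is unknown. Someone with no test and no code stays in the denominator and is indistinguishable from someone tested and found normal. That does little harm if the share of such patients is the same in every group being compared. The article's own account of DOACs gives a reason to think it may not be: a prescriber considering a DOAC has more cause to look at renal function than one considering warfarin or no treatment.

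Two results depend on this. Objective 3 asks whether renal impairment goes with being started on a DOAC, on warfarin or on nothing, and part of any difference could reflect who was tested. Objective 4 then adjusts its Cox model for important covariates identified in Objective 3, so a distorted comparison can affect which covariates enter, and the covariate itself carries the misclassification.

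The article recognises the same kind of problem elsewhere. It drops the labile INR element from HAS-BLED partly because DOAC users would not have that test. The renal covariate has no comparable safeguard.

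**Working it through.** The article states no renal prevalence, testing rate or coding rate, so there is no figure to reproduce. The arithmetic below only illustrates the possible size.

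**Inputs, all assumed**
- p: true prevalence of impairment, 30% to 50%, first taken as equal in both groups.
- t: share with a usable renal test. Starters v untreated: 95% v 95%, 98% v 95%, 95% v 85%, 95% v 70%.
- c: chance that an untested impaired patient carries a code, 0.3 to 0.9.
- f: chance that an untested unimpaired patient carries a code, 0 to 0.10.
- A test is taken to give the true status, as the article lets it decide.

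**Formula**

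Recorded prevalence = p × [t + (1 − t) × c] + (1 − p) × (1 − t) × f

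With equal p in both groups, the false difference (starters minus untreated) is

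(t_starters − t_untreated) × [p × (1 − c) − (1 − p) × f]

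**No wrong codes (f = 0)**

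| Tested, starters v untreated | Smallest (p = 0.30, c = 0.9) | Largest (p = 0.50, c = 0.3) |
|---|---|---|
| 95% v 95% | 0 | 0 |
| 98% v 95% | 0.03 × 0.30 × 0.1 = 0.1 points | 0.03 × 0.50 × 0.7 = 1.1 points |
| 95% v 85% | 0.10 × 0.30 × 0.1 = 0.3 points | 0.10 × 0.50 × 0.7 = 3.5 points |
| 95% v 70% | 0.25 × 0.30 × 0.1 = 0.8 points | 0.25 × 0.50 × 0.7 = 8.8 points |

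A middle case at p = 0.40, c = 0.3, 95% v 70%: 0.40 × (0.95 + 0.05 × 0.3) = 38.6% against 0.40 × (0.70 + 0.30 × 0.3) = 31.6%, a difference of 7.0 points where the true difference is nil.

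**Tests also clear wrong codes (c = 0.9, f = 0.10, 95% v 70%)**
- p = 0.30: 0.25 × (0.03 − 0.07) = −1.0 point
- p = 0.40: 0.25 × (0.04 − 0.06) = −0.5 points
- p = 0.50: 0.25 × (0.05 − 0.05) = 0

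The artefact can vanish or change sign.

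**A true difference in the other direction (f = 0; tested 95% v 85% or 95% v 70%; c = 0.3 to 0.9)**
- True 35% in starters v 45% in untreated: observed −1.8 to −9.5 points. The difference is attenuated but not reversed in any scenario run.
- True 40% v 45%: observed −4.5 to +3.1 points. The reversal arises at 95% v 70% with c = 0.3: 0.40 × 0.965 = 38.6% against 0.45 × 0.79 = 35.5%.

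**The case against.** Several points on the other side stand.

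- A reader might infer that every untested patient counts as unimpaired. The article does not say so: an untested patient with a chronic kidney disease or renal impairment code is impaired in the stand-alone covariate. The only explicit rule of this kind, "If there are no test results recorded, the patient will score 0", is in HAS-BLED and covers only a renal impairment code without severity.
- A reader might infer that renal testing goes with starting any anticoagulant. No section says that. The sentence on DOACs concerns adjustment and monitoring in patients who are already impaired, so testing at initiation is an inference with some support for DOACs and none for warfarin. Period 1 (2003–2007) precedes DOACs, so the argument has little hold there.
- No look-back limit is set, so any usable test on record may count, and the gap in tested shares may be small. Untreated patients are assessed at the end of the period, which gives them extra time to collect tests and codes. This works against the suggested direction.
- Whether a table carries a row for unknown status is often left to a fuller document, and the Missing data section does not claim that all other variables are complete. The Discussion also concedes that comorbidities may be under-recorded.

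The last point has limits. The article itself fixes the classification rule, the denominator and the list of incomplete variables, and together these treat no information as no impairment. The Discussion argues that chronic conditions are likely to be recorded accurately, which does not cover a status that can come from a test result alone.

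It is also tempting to make tested patients the main comparison. That can be worse. Suppose true prevalence is 40% and untreated patients are tested in 85% of impaired and 60% of unimpaired cases (assumed). The tested share is 0.40 × 0.85 + 0.60 × 0.60 = 70%, and tested-only prevalence is 0.34 / 0.70 = 48.6%, an error of 8.6 points. The existing rule with half of impaired patients coded gives 0.40 × (0.85 + 0.15 × 0.5) = 37.0%, an error of 3.0 points.

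**Conclusion.** The concern holds as a risk of differential ascertainment that the plan cannot detect as written. Patients with neither a test nor a code are counted as unimpaired, renal tests are outside the named incomplete variables, and the article's own reasoning makes more complete ascertainment in DOAC starters plausible.

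The stronger claim, that starters will look more impaired by detection alone, is not supported. Size and sign depend on testing and coding rates that the article does not give. With equal true prevalence of 30% to 50%, the artefact runs from 0 with equal testing to 8.8 points at 95% v 70% tested with poor coding, and to −1.0 point if tests also clear wrong codes. A true deficit of 10 points in starters survived every scenario run; one of 5 points could be hidden or reversed. The inference from DOAC monitoring to more testing applies mainly to periods in which DOACs were prescribed.

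**What to change.** 1. In each group and time period, report renal status as impaired (by stage), tested and not impaired, or no test and no code, and show the tested share.
2. Keep the full-cohort comparison as the main one.
3. Add two sensitivity analyses: one restricted to tested patients, with the same look-back before the relevant date in all groups, and one using codes only. If all three agree, detection is an unlikely explanation for a difference.
4. Add creatinine and eGFR to the incomplete variables in the Missing data section.

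The data are already to be extracted. The cost is a few extra table rows and two sensitivity analyses, of which the tested-only one describes a selected subset and should be labelled so.
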